# Effects of exercise prehabilitation before anterior cruciate ligament reconstruction on functional outcomes during pre- and postoperative rehabilitation — protocol for a single-blinded randomised controlled trial

**DOI:** 10.1186/s13063-023-07776-1

**Published:** 2023-11-24

**Keywords:** Knee, Prehabilitation, Preoperative training, ACL, RCT, Intervention

## Abstract

**Background:**

Although a benefit of preoperative training prior to anterior cruciate ligament (ACL) reconstruction is likely, there is no consensus on the optimal content (criteria-based programme), supervision (one-on-one guidance or self-administered training) and general setting of preoperative training after ACL injuries. The purpose of this trial is to investigate the efficacy of an individually adaptive, guided, structured and criteria-based preoperative rehabilitation programme in comparison to a non-guided and self-administered home training programme.

**Methods:**

The planned single-blinded randomised controlled trial study was approved by the ethics committee of the German Sport University on June 14, 2022 (ethics application no. 093/2022) and prospectively registered (DRKS-ID: DRKS00030312; date of registration: 26.09.2022). *N* = 114 participants between 16 and 60 years of age with a unilateral ACL rupture and scheduled ACL reconstruction with a hamstring or quadriceps tendon autograft will be randomly (block-randomisation, 1:1 allocation) and blinded assigned to one of two groups: intervention group (structured, criteria-based, guided prehabilitation training) and comparator group (non-guided, self-administered home training). After surgical reconstruction, patients of both groups participate in the same standard, functional measurement-guided, postoperative rehabilitation programme. Stepwise increasing the functional requirements of the assessments, all participants participate in testing at the day of anamnesis (t1), 1–7 days before surgical reconstruction (t2), day of surgical reconstruction (t3) and 30 (t4), 60 (t5), 90 (t6) and 180 (t7) days post-reconstruction.

The primary outcome is the overall self-reported knee condition, assessed by the sum score of all sub-scales of the Knee injury and Osteoarthritis Outcome Score (KOOS). Secondary outcomes include functional outcomes (range of motion, knee flexors and extensors and plantar flexors strength/torque, functional postural control, jumping ability), workability and return to sport (RTS) (psychological readiness, RTS success).

**Discussion:**

The planned study targets to fill a gap in the evidence regarding effective designs of prehabilitation training before surgical ACL reconstruction. Potential difficulties that could affect the conduct of the study are lack of treatment adherence of the patients and high dropout.

**Trial registration:**

German Register of Clinical Trials DRKS-ID: DRKS00030312. Registered on 26 September 2022.

**Supplementary Information:**

The online version contains supplementary material available at 10.1186/s13063-023-07776-1.

## Background

The rupture of the anterior cruciate ligament (ACL) is one of the most common and severe knee injuries [1–3]. Athletes are more endangered to rupture their ACL than inactive individuals [1–3]. In particular in such active patients, the surgical reconstruction of the ACL is the evidence-based rehabilitation and most common treatment after an ACL rupture [4, 5].

Ruptures of the ACL often lead to knee osteoarthritis and secondary instability in the knee joint [6]. Athletes returning to sports after ACL injury have a up to six-fold increased probability of recurrent injury up to 2 years postoperative compared to non-injured athletes [7]. They often perform worse and are characterised by shorter careers than non-injured counterparts [8]. These secondary and follow-up issues often occur after surgical reconstruction despite evidence-based treatments. As a consequence, the rehabilitation process after ACL injuries can still be improved in order to restore the function of the knee and to maintain physical activity and workability. The latter may vice versa lead to a decreased secondary issue or re-injury risk [9]. Clinical practice guidelines for anterior cruciate ligament rehabilitation recommend to include a prehabilitation phase between the injury and the reconstruction [5]. The suggested benefit of preoperative rehabilitation (prehabilitation) is based on the “better-in better-out” strategy. For example, the preoperative maintenance/improvement of conditional and coordinative performance, the improvement of perceived self-efficacy and the reduction of risk factors should enhance the pre- and postoperative functional outcomes and postoperative recovery [10]. The time between injury and reconstruction can vary from a few hours to several months. The later the surgery, the more time there is for preoperative preparation. Most patients are eligible for individually modified preoperative training after the inflammatory phase has ended (about 1 week after injury) [11].

But high-quality evidence investigating preoperative training is sparse. There is only low- to moderate-quality of evidence that prehabilitation approaches, in particular preoperative functional training, have a positive impact on preoperative and postoperative functional performance [12]. And there is only low-quality evidence that preoperative training has a positive effect on quadriceps strength, on performance in single-leg hop jumps 3 months postoperatively, and on self-perceived knee function and faster return to competition [12, 13]. Furthermore, there is no evidence-driven consensus regarding optimal content, supervision (one-on-one guidance or self-administered training) and general settings of preoperative training [12–14]. The available studies often lack an adequate comparator group, a sufficient follow-up time or important outcomes to provide evidence on the relevance of preoperative rehabilitation measures of potential secondary issues [12, 13].

## Methods

### Aims

The planned study focusses on optimal content (criteria-based programme), general setting of preoperative training and supervision (one-on-one guidance or self-administered training). With this randomised-controlled trial, our objective is to compare the effects of a guided, structured and criteria-based preoperative rehabilitation programme, which can be adapted to the individual performance level, to a non-guided and self-administered home-based training programme on functional and self-report outcomes and secondary issues (other knee function, daily living and return to sport). The KOOS sum score (Knee Injury and Osteoarthritis Outcome Score) is the primary outcome and assesses the self-perceived knee function [15, 16]. We hypothesise that the guided prehabilitation programme will be more effective than self-administered home training relating to its effect on the baseline to pre-reconstruction change score of the KOOS sum score.

We will investigate the effects of pre-operative training (guided vs. unguided) at different time points (pre-op, 30/60/90/180 days post-op). We expect that the guided prehabilitation programme will have a particularly positive short-term effect and that the difference between the two groups will decrease over the progress of rehabilitation.

### Study design

This study is a monocentric, prospective randomised controlled single-blinded (patient-blind) trial. All patients receive an intervention, they do not know which group they are part of (intervention or comparator group). Ethical approval has been provided by the independent ethics committee of the German Sport University on June 14, 2022 (ethics application no. 093/2022). The study is prospectively registered (DRKS-ID: DRKS00030312; date of registration: 26.09.2022). The study was planned and performed in agreement with the Declaration of Helsinki (Version Fortaleza 2013). All adverse events will be reported. Informed consent is obtained by each participant prior to study enrolment. The protocol corresponds to the Standard Protocol Items of Recommendations for Interventional Trials (SPIRIT) guidelines (SPIRIT 2013 checklist) [17] (Fig. 1).

**Fig. 1 Fig1:**
[figure not shown]
Schedule of enrolment, interventions and assessments (SPIRIT 2013, Standard Protocol Items: Recommendations for Interventional Trials) (t1 = first ambulant presentation in the hospital with confirming the diagnosis, selection of the operator and scheduling the operation, t2 = 1–7 days before surgery, t3 = surgery day, t4 = 30 days post OP, t5 = 60 days post OP, t6 = 90 days t7 = 180 days post OP)

### Interventions

#### Prehabilitation programme (intervention group)

During the period between injury and surgical reconstruction, the participants of the intervention group perform a structured, criteria-based, guided training at PhysioSport PACE GmbH. The training programme will be adapted to the individual performance level and consists of two training sessions of 60 min per week. In addition, participants receive exercises once a week for self-administered training at home.

The prehabilitation programme is increased progressively and includes the following components [12, 18]Mobilisation of the knee joint, improvement of mobilityImprovement of neuromuscular control, especially of the musculus quadricepsImprovement of postural stability and balanceRestoration or increase of muscle strength (especially knee flexors and extensors, abductors, plantar flexors; local muscle strength endurance training, increase of muscle section, increase of neuromuscular strength).

The choice of exercises is consistent with the exercises in previous studies [12]. In our planned trial, the prehabilitation programme is criteria-based and includes exercises at two levels (level I and level II). The exercise selection and progression are shown in Fig. 2.

**Fig. 2 Fig2:**
[figure not shown]
Exercise selection of the prehabilitation programme (level I and level II), recommended number of repetitions and adaptation possibilities of the exercises to lower/higher performance levels (ROM = range of motion, VAS = visual analogue scale, rep. = repetitions)

At the beginning therapists at PhysioSport adapt exercises from level I to the individual performance level of the participants. If the participants have full, active knee joint extension, no tissue reaction on the following day of training (at least two consecutive training sessions) and no painful movement restrictions during the exercises (visual analogue scale (VAS) of 0–10 for subjective measurement of pain, VAS < 3–4), the exercise selection can be extended or replaced with exercises from level II by the therapist.

There is no time limit for achieving a level and differences in participants’ performance are to be expected. Therefore, it is conceivable that participants do not perform all the exercises of level II prior to surgical reconstruction and only perform the exercises from level I. The training programme aims to increase individual performance and not to achieve a defined performance level.

The therapists prospectively document the type, intensity, frequency and duration of all training sessions at PhysioSport, the self-administered training sessions performed at home and other treatments (e.g. physiotherapy) or unintended effects.

#### Comparator: self-administered home training

In clinical care, the patients usually do not receive any supervised, criteria-based, active therapy prior to surgical treatment. They are most often only asked to exercise on their own. The participants in the comparator group are also asked to exercise on their own and receive a brochure containing six exercises (active knee extension, single leg stands, external hip abduction, hip bridge in the back position, calf lift double legged, squats). These exercises pursue the same goals as the exercises in the guided prehabilitation programme. Participants find information in the brochure about the execution of the exercises and the number of repetitions. The brochure also contains information on the progression of the exercises. As they are all based on usual care exercises, the selection of the exercises and their progression are accompanied by a low risk of injury and follow the same principles as those in the intervention group. The treating physicians at the hospital recommend the participants of the comparator group to perform the exercises three times a week as self-administered, preoperative home training. The participants document independently all self-administered training sessions and other unintended effects. Patients will present this protocol to PhysioSport at preoperative testing. If participants have any questions, they can contact the study management. The self-administered training was chosen as the comparator to investigate the general setting and supervision (one-on-one guidance or self-administered training) of preoperative training after ACL injuries in this trial.

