**Fig. 3 Fig3:**
[figure not shown]
Study flow chart: study procedure (enrollment, allocation, pre-surgery follow-up, post-surgery follow-ups) (ACL = anterior cruciate ligament)

Prior to surgical reconstruction (1–7 days before surgical reconstruction), the participants of both groups perform tests to assess the functionality of the knee joint guided by a therapist and complete selected questionnaires. Selected functional tests directed by a physician in the hospital and a questionnaire survey are also performed on the day of surgical reconstruction (postoperatively). There will be no special criteria for discontinuing or modifying allocated interventions. Patients will not be excluded from the study based on intention to treat. However, non-compliance will be monitored and reported.

While the prehabilitation programmes differ before surgery (guided training vs. home training), all participants participate in a standardised rehabilitation programme at PhysioSport after surgical reconstruction (Fig. 3).

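### Before surgery, home training, other treatments and unintended effects are recorded by therapists in one arm and by patients in the other, so reported harms and non-compliance are open to differential ascertainment

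*Protocol article*

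**What the plan says.** For the intervention arm, the section on the prehabilitation programme (text after Fig. 2) states: "The therapists prospectively document the type, intensity, frequency and duration of all training sessions at PhysioSport". The same sentence extends the therapists' record to "the self-administered training sessions performed at home and other treatments (e.g. physiotherapy) or unintended effects". Staff contact is frequent, because the programme "consists of two training sessions of 60 min per week".

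For the comparator arm, the section on self-administered home training gives the recording task to the patients, and staff see the result once: "The participants document independently all self-administered training sessions and other unintended effects. Patients will present this protocol to PhysioSport at preoperative testing". Patients may contact study management if they have questions. Other treatments are not mentioned for this arm.

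Two commitments draw on this kind of information. Study design says "All adverse events will be reported", and Study procedure says "However, non-compliance will be monitored and reported". The article describes no common form and no common way of asking about these items before surgery.

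**The concern.** Home sessions, treatment obtained elsewhere and unintended effects can occur in both arms. To compare them between arms, they have to be collected in the same way. Here the person recording and the opportunity for staff to prompt, clarify or notice something are set differently by arm. An analysis plan cannot repair this afterwards, because the difference lies in how the data were obtained.

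Three things are at stake:

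- **Harms.** A difference in the number of unintended effects before surgery could reflect the method of recording, the training, or both.
- **Compliance.** The Discussion itself names lack of motivation as a risk in the comparator arm. That is the arm whose training record staff first see when the preoperative training is nearly over.
- **Co-treatment.** The trial asks whether guidance adds something. Physiotherapy obtained elsewhere is the co-treatment most relevant to that contrast, and it is a named item only where guidance is already provided.

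**Working it through.** The plan gives no figure for this point, so the check sets the two recording rules side by side.

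| Item | Intervention arm | Comparator arm |
|---|---|---|
| Who records | Therapist | Patient |
| When staff see the information | Two scheduled sessions a week | Once, at preoperative testing (t2) |
| Guided sessions | Logged in detail | Not applicable |
| Home sessions | Named | Named |
| Other treatments, e.g. physiotherapy | Named | Not named |
| Unintended effects | Named | Named |

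The guided-session row differs by design and is no fault. The last three rows concern things that can happen in both arms.

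**Scheduled staff contacts before t2.** The inputs are 2 sessions a week (Prehabilitation programme), at least 3 weeks of training (Study procedure), an injury-to-surgery window of 3 to 13 weeks (inclusion criteria), and t2 at 1 to 7 days before surgery.

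- Minimum training of 3 weeks: 2 × 3 = 6 sessions up to surgery. With t2 a full week earlier, 2 × (3 − 1) = 4. So about 4 to 6.
- Upper bound of 13 weeks: 2 × 13 = 26, or 2 × (13 − 1) = 24 with t2 a week earlier. This is a ceiling, since training cannot start on the day of injury.
- Comparator arm: one handover of the record. This counts staff contacts with the record, not entries, because patients are asked to write down every session.

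**What unequal capture could do.** The article gives no capture rates, so the following values are assumptions for illustration only. Let the true risk of an unintended effect be the same in both arms, p = 20%, with 57 patients per arm (Sample size determination). Expected recorded events = 57 × p × capture.

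- Therapist capture 90%: 57 × 0.20 × 0.90 = 10.3.
- Diary capture 70%: 57 × 0.20 × 0.70 = 8.0; apparent ratio 0.90/0.70 = 1.29.
- Diary capture 50%: 57 × 0.20 × 0.50 = 5.7; apparent ratio 0.90/0.50 = 1.80.
- Reversed, therapist 70% and diary 90%: 8.0 against 10.3; apparent ratio 0.70/0.90 = 0.78.

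The ratio depends only on the two capture rates, not on p. It can fall on either side of 1, so the direction is open. The same holds for compliance: a self-kept record can overstate sessions or leave them out.

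**Primary outcome.** KOOS is a patient questionnaire given to both arms. Neither its analysis nor the sample size of 114 uses the training records.

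**The case against.** The best counter-argument has four parts.

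1. **Different recorders follow from the question.** Only supervised patients have a therapist present. This holds for the guided sessions. It does not hold for home sessions, outside treatment and unintended effects, which both arms could record on the same form. Therapists cannot watch home sessions, so their entries presumably rest on what patients tell them. The remaining difference is who writes the entry and how often the patient is seen. That still matters for ascertainment.

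2. **The comparator record gets one condensed sentence.** Its fields are not listed, and the diary may well include other treatments. This stands in part. A reader might infer that outside physiotherapy in the comparator arm goes unrecorded, but the article does not say so. It supports only that the item is named for one arm, so comparable capture is not assured.

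3. **No formal comparison is at risk.** Harms, adherence and co-treatment are not listed as outcomes, and the Statistical analysis section plans no test of them. This limits the weight of the point. The promise to report adverse events and non-compliance remains, and readers will compare the arms.

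4. **The stronger inferences do not follow.** A reader might conclude that unintended effects will look more frequent in the guided arm. The article describes documentation, not repeated questioning, and the direction cannot be derived. A reader might also conclude that a null KOOS result could not be interpreted because comparator patients were guided elsewhere. Any shrinkage of the KOOS difference would come from the contamination itself and would be the same with a perfect diary. The article gives no rate for it and says that supervised therapy before surgery is not usual care.

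**Conclusion.** The point holds as a defect in the collection of process and safety data before surgery. It rests on two stated rules that differ by arm in recorder and in frequency of staff contact: about 4 to 6 scheduled contacts before t2 at the minimum training length, against one handover. The naming of other treatments for one arm only is weaker support, because the article may condense the diary's content.

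Between-arm statements on unintended effects, home training and co-treatments are open to differential ascertainment of unknown size and direction. The illustrative ratios rest wholly on assumed capture rates. The primary KOOS test and the sample size are not affected. The change is worth making because it is cheap and the data cannot be corrected later, but it does not threaten the main result.

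**What to change.** - Give patients in both arms one identical diary for everything done outside PhysioSport before surgery: home sessions (with the same fields in each arm), other treatments including physiotherapy, and unintended effects.
- Collect it at the existing t2 visit in both arms, with the same short set of structured questions on unintended effects and other treatments.
- Keep the therapist log of guided sessions as an additional record that describes the delivered programme.
- State that between-arm comparisons of home training, co-treatments and harms before surgery use the common instrument only.

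The cost is a revised diary page and a few questions at a visit that already takes place, with slightly more form-filling for patients. Recruitment began on 01/04/2023, before the protocol date of 22/06/2023, so patients already enrolled will have the old-format record. They should be identified as such when these data are reported. No visit, treatment rule, sample size or primary analysis changes.

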### Postoperative rehabilitation programme

After surgical treatment participants of both groups participate in a standard, guided, postoperative rehabilitation programme at PhysioSport. The rehabilitation programme initially focuses on postoperative follow-up treatment (wound and scar treatment, reduction of swelling, etc.). Subsequently, the goals already defined in the prehabilitation phase are pursued (mobilisation of the knee joint/ improvement of mobility, improvement of neuromuscular control especially of the m. quadriceps, improvement of postural stability/balance, restoration/increase of muscle strength). Monitoring of rehabilitation ends 180 days after surgery.

### Sample — inclusion criteria

Persons aged 16–60 years with unilateral and total primary ACL rupture (confirmed by magnetic resonance imaging) with indication for an arthroscopically assisted, anatomic ACL reconstruction using a hamstring or quadriceps tendon autograft who will be operated at Sana Medical Centre Cologne (inpatient or outpatient) are screened for inclusion. Participants can be included if the length of the period between injury and surgery is at least 3 and no longer than 13 weeks. Only participants who are able to give consent will be included. A parent or guardian must also sign the consent form for non-adult participants (16 or 17 years of age).

